##### 2.3.5.3. Retinal vascular evaluation

Nasal and temporal images centered in the papilla, taken in a sitting position, will be obtained by a trained nurse using a non-mydriatic retinograph, TOPCON TRC NW 200 (Topcon Europe BC, Capelle aan den IJssel, The Netherlands). Using the ALTAIR software (registry entry 00/2015/995) specifically developed by our group, vessel thickness, area, and length of the retina were then calculated semiautomatically (46).

##### 2.3.5.4. Cognitive assessment

The Montreal Cognitive Assessment (MoCA), validated in Spain (47), will be used to evaluate cognitive impairment. The MoCA assesses several cognitive domains: attention and concentration, executive functions, memory, language, visuoconstructional skills, conceptual thinking, calculations, and orientation. The total possible score will be 30 points; a score of 26 or above will be considered normal. The time estimated for MoCA administration will be approximately 10 min.

#### 2.3.6. Laboratory measurements

Venous blood samples will be collected between 08:00 and 09:00 after fasting for 12 h. A complete blood count, fasting plasma glucose, creatinine, uric acid, liver function, lipids, inflammatory markers, and thyroid function will be measured using standard automated enzymatic methods. A blood sample from each participant will be frozen for subsequent evaluation of total bile acids, deoxycholic acid, and SCFA concentration (mg/mL).

#### 2.3.7. Gut and oral microbiota measurements

Participants will collect stool samples using the OMNIgene GUT (OMR-200) kit, which allows transport and storage while ensuring that stabilized DNA is preserved so that the *in vivo* microbiota profile will be accurately represented. The OMNIgene GUT kit is an easy self-collection system, enabling participants to properly collect their own samples at home following the manufacturer's recommendations. This kit minimizes bias introduced by microbial growth and DNA degradation, obtaining high-quality DNA appropriate for 16S rRNA gene microbiome profiling. During the study visit, unstimulated saliva samples will also be collected by spitting into a sterile 50 ml Falcon tube (*GenoChem World*). Subsequently, 2 ml of this sample will be transferred with a sterile pipette to two different and clearly labeled microtubes (*criogenic vial*), with 1 ml in each microtube. Once stool and saliva samples have been collected, they will be frozen at−20°C and sent to the Cancer Research Institute, maintaining the storage conditions.

According to the manufacturer's instructions, DNA will be extracted from a total volume of 100–150 ul of each feces sample using the FastDNA Soil kit [FastDNA^®^ SPIN Kit for Soil (MP Biomedicals, USA)]. Each sample volume will be added together with MT buffer and sodium phosphate buffer to a Lysing Matrix E tube (each tube contains 1.4 mm ceramic spheres, 0.1 mm silica spheres, and one 4 mm glass bead). This mixture will be homogenized for 40 s at 6 m/s in the FastPrep-24^TM^ 5G bead-beating grinder and lysis system, enabling a mechanical disruption of the living organisms' cell walls while protecting and solubilizing nucleic acids. DNA from saliva samples will be extracted with the MagNA Pure LC 2.0 Instrument (Roche Diagnostics, Barcelona, Spain) using the MagNA Pure LC DNA Isolation Kit III for Bacteria and Fungi (Roche Diagnostics GmbH) following the manufacturer's instructions with an additional enzymatic lysis step with lysozyme (20 mg/ml, 37°C, 60 min; Thermomixer comfort, Eppendorf), lysostaphin (2,000 units/mg protein, 37°C, 60 min; Sigma-Aldrich) and mutanolysin (4,000 units/mg protein, 37°C, 60 min; Sigma-Aldrich), following Dzidic et al. (48). DNA will be eluted with 50–150 ul of DNase/Pyrogen-Free Water (DES). Nanodrops will then be used to spectrophotometrically measure purified DNA yield (ng ul-1) and verify its quality and quantity. Low absorption ratios at 260/230 nm (<2) will be used as a marker for contamination from polysaccharides, and low absorption ratios at 260/280 nm (<1.7) will be used to identify protein impurities. Additionally, it will be fluorometrically quantified in a Qubit 4.0 fluorometer (Invitrogen, USA), and DNA integrity will be analyzed in a TapeStation 4,200 using Genomic DNA ScreenTapes (Agilent, USA). A high DNA integrity number (DIN) indicates large DNA fragments, whereas a low DIN indicates more fragmented DNA. The DIN scale ranges from 1 to 10.

##### 2.3.7.1. Amplicon library and Illumina sequencing of bacterial 16S rRNA genes

The 16S rRNA gene has been a mainstay of sequence-based bacterial taxonomic analysis for decades (49, 50). Variable regions v3-v4 have been shown to have an excellent resolution for phylogenetic classification, and their appropriate size for Illumina library preparation has made them the preferred region for high-throughput bacterial composition studies. However, some bacterial genera, such as *Streptococcus*, have been shown to be 100% identical in that region (48), and other bacterial genera, especially those with high G+C content, such as *Bifidobacterium*, have been shown to be under-amplified by the Illumina V3-V4 primers (51). In addition, variable regions v4-v6 have also been identified as the most functional regions in other studies (52). To select an appropriate region for our samples, we will perform a pilot study where 50 samples were amplified and sequenced using the V3-V4 and the V5-V6 regions. The corresponding taxonomic assignment showed high congruency between the two regions, with correlation coefficients of 0.957 to 0.979 at the genus level and 0.980 to 0.995 at the phylum level (*p* < 0.001 for all), indicating that both regions would provide similar bacterial composition assessments. However, 75% of the samples provided higher sequencing output using the V5-V6 region, with 25% of the samples reaching over 100,000 reads (vs. 4% when using the V3-V4 region). This would likely provide a complete assessment of bacterial richness and diversity, as low-frequency bacteria would only be detected with high sequencing coverage. On this basis, we selected the V5-V6 regions to be sequenced in this protocol.

Primers were taken from Gohl et al. (53) being the sequence: V5F_Nextera 5′-RGGATTAGATACCC-3′ and V6R_Nextera 5′-CGACRRCCATGCANCACCT-3′. These primer pairs have added Illumina adapter overhang nucleotide sequences:

ü Forward overhang: 5′ TCGTCGGCAGCGTCAGATGTGTATA AGAGACAG-[locus-specific sequence].ü Reverse overhang: 5′ GTCTCGTGGGCTCGGAGATGTGTAT AAGAGACAG-[locus-specific sequence].

First, each sample will be amplified using these bacterial primers with Illumina adapters, as described above. Agencourt AMPure XP (Beckman Coulter) will be used to purify the resulting amplicons, which will then be amplified in a subsequent PCR where indexes are added. A different index sequence will be used to identify each sample from each patient. Finally, these indexed amplicons will be purified using the Agencourt AMPure XP kit. Amplicon libraries for each sample will then be generated. Equimolar amounts of these libraries should be pooled, normalized, and quantified in the Qubit. The pooled samples will be sequenced using an Illumina MiSeq platform (2 × 300 bp v3 chemistry).

### 2.4. Bioinformatics and statistical analysis

The data will be registered using the REDCap platform (Research Electronic Data Capture) (54, 55). The Kolmogorov-Smirnov test will be used to verify the normal distribution of the variables. Raw sequence data will be analyzed using an *in-house* pipeline. Quality passing-filter readings will be clustered into operational taxonomic units (OTUs). Quality control will be carried out on a *per-sample* basis, discarding paired ends with an overlap of <200 nt and removing chimeric sequences using *de novo* chimera detection in USEARCH (56). To analyze differences between qualitative variables, an X^2^ test will be used. To analyze the difference in means between quantitative variables in two categories, the Student's *t*-test or the Mann–Whitney U-test will be used, as appropriate. If the qualitative variable has more than two categories, an analysis of variance (ANOVA) will be used, and the results will be adjusted for the false discovery rate (FDR) using the Benjamin and Hochberg method. A *p*-value of 0.05 adjusted for FDR will be considered statistically significant. The Kruskal–Wallis test will be used if the variables are not normally distributed. An analysis of covariance (ANCOVA) will be performed to adjust for variables that may affect the results as confounding factors. The association of quantitative variables will be analyzed using Pearson's or Spearman's correlation test. We will fit linear or penalized multivariate logistic models using the Least Absolute Shrinkage and Selection Operator (LASSO) method (57), which can be applied to high-dimensional data to analyze the relationships between lifestyle variables and aging arterial, cardiovascular, and neurocognitive health status, as well as microbiota variables.

Given the compositional nature of microbiome data (58, 59), an ANCOM-BC method will also be used to identify significant differences in bacterial composition between groups and for frequency normalization. Linear discriminant analysis (LDA) effect size (LEfSe) will be used to identify differentially abundant taxa between groups using the Kruskal–Wallis test *P* < 0.05. These data will be validated using edgeR differential abundance analysis (false discovery rate adjusted *P* < 0.05 on species) on MicrobiomeAnalyst (60, 61). Further analyses will be performed using MicrobiomeAnalyst from the rarefied samples, including α and β diversity, abundance profiling, and clustering analysis. In the microbiota analysis, alpha, beta, and gamma diversity parameters will be estimated. Additionally, richness and equality parameters such as Chao1, Shannon, Simpson, and Pelou will be calculated. A description of all parameters will be developed, as will an exploratory analysis of the microbiota using graphs of abundance, richness, heatmaps, and phylogenetic graphs, as well as cluster analysis. Comparisons of diversity and taxa between groups will be made using the Welch test, Wilcoxon test, chi-square test (presence/absence), ANOVA procedure with Tukey's multiple comparisons, and Kruskal–Wallis test with FDR multiple comparisons, as appropriate. An exploratory compositional analysis of the microbiota will be carried out using biplot graphs, scree plots, dendrograms, and bar plots. The composition of the microbiota between groups will be compared using parametric procedures such as the *t*-test or ANOVA or non-parametric procedures, adjusting for multiple comparisons. To analyze the association of the microbiota with different groups with a multivariate approach, Zero-Hurdle Poisson Models (ZHP) will be adjusted given the predicted presence of excess zeros and overdispersion in the data. To analyze the associations between oral and intestinal microbiota and various groups, the Zero-Inflates Beta Regression Model (ZIBR) will be adjusted with random effects due to the predictable autocorrelation between the samples of the two microbiotas. To compare bacterial diversity between oral and gut samples, we will use Chao1 and Shannon index analyses using the same number of sequences per sample to control for biases in the estimations of richness and diversity, as described in Havsed et al. (62). To compare bacterial composition between oral and gut samples, paired samples will be used to study the correlations in bacterial levels intra- and inter-niche. To study the correlations among the bacteria, unsupervised sPCA from the mixOmics R package will be performed. A multivariate analysis (sPLS-canonical) from the mixOmics R package will also be applied using as input the normalized dataset of all bacteria counts, following Rohart et al. (63). Correlations will be conducted not only between bacteria but also between bacteria and different continuous variables, as described in Havsed et al. (62). Specifically, we will use sparse partial least squares (sPLS) to perform simultaneous variable selection in the two datasets (bacterial species abundance and quantitative variables). These associations will be plotted using heatmaps and networks with the mixOmics R package (63).

To examine whether the association between lifestyle and arterial aging is mediated by the intestinal microbiota, linear regression models will be fitted using bootstrapped mediation procedures included in the PROCESS SPSS macro (64). All variables will be analyzed disaggregated by sex, and differences with a gender perspective will be analyzed where appropriate since the influence of gender in many pathologies is known, particularly in cardio and cerebrovascular diseases.

The analyses will be conducted using the R v.4.2.1 program (65). R: A language and environment for statistical computing. R Foundation for Statistical Computing, Vienna, Austria (https://www.R-project.org/) and the statistical package SPSS for Windows version 28.0. (IBM, Armonk, New York: IBM Corp). A value of *p* < 0.05 will be considered statistically significant. Statisticians/researchers who perform different analyses will be blinded to patients' clinical data.

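### LEfSe flags taxa at an unadjusted P < 0.05 while FDR is used elsewhere; the edgeR step covers species only, is not an independent validation, and is not required before a taxon is reported

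*Protocol article*

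**What the plan says.** All statements are in Section 2.4 (Bioinformatics and statistical analysis) of the protocol article.

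- **First paragraph.** After the sentence on variables with more than two categories, it sets a rule: "A *p*-value of 0.05 adjusted for FDR will be considered statistically significant".
- **Second paragraph, compositional method.** "an ANCOM-BC method will also be used to identify significant differences in bacterial composition between groups". No threshold is given for it.
- **Second paragraph, LEfSe.** Taxa are identified by LDA "effect size (LEfSe) will be used to identify differentially abundant taxa between groups using the Kruskal–Wallis test *P* < 0.05". No adjustment is mentioned.
- **Second paragraph, edgeR.** "These data will be validated using edgeR differential abundance analysis (false discovery rate adjusted *P* < 0.05 on species". No second sample or data split is described.
- **Second paragraph, other comparisons.** Diversity and taxa are compared by several tests, including "ANOVA procedure with Tukey's multiple comparisons, and Kruskal–Wallis test with FDR multiple comparisons, as appropriate". Composition is compared by "parametric procedures such as the *t*-test or ANOVA or non-parametric procedures, adjusting for multiple comparisons".
- **Final paragraph.** "A value of *p* < 0.05 will be considered statistically significant", with no scope and no mention of adjustment.

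The abstract names LEfSe and ANCOM-BC as the methods for finding differentially abundant taxa and does not mention edgeR.

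**The concern.** Within one paragraph, a Kruskal–Wallis test of taxa between groups carries two cut-offs: raw 0.05 inside LEfSe, and FDR-adjusted elsewhere. The edgeR sentence spells out its FDR adjustment, so the absence of one in the LEfSe sentence reads as a stated threshold, not as shorthand.

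The edgeR step does not settle this, for three reasons:

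- It is specified for species. LEfSe is specified for taxa generally, and the pilot in Section 2.3.7.1 reports at genus and phylum level.
- As far as the text shows, it uses the same participants. It is a second method, not an independent validation.
- Nothing says that a taxon must pass it before being reported.

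Two analysts could both follow the article and publish different lists of taxa, one of them without error control. The link between lifestyle and microbiota is the main objective, and Section 4 (Summary) presents the project as the first phase of future intervention trials. The list of taxa is therefore a result that others will build on.

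**Working it through.** **What the article supplies.** The LEfSe cut-off (0.05, unadjusted), the edgeR cut-off (FDR 0.05, species) and the two significance sentences. It gives no number of taxa, no share of taxa with no true difference, no power per taxon and no false share, so there is no stated figure of this kind to reproduce.

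The article's only comparable error-rate calculation is in Section 2.2: alpha 0.05 two-sided, power 0.80, SD 0.4, difference 0.1, 30%/70% split, 5% dropout. It gives 180 and 420, or 190 and 443 after dropout, against the stated 190 and 436. That is close, but it concerns a single Shannon-index test and says nothing about taxa tested in bulk.

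**Step 1: LEfSe alone.** With null share π₀ and power w per taxon, and P < 0.05 as the only filter:

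false share = 0.05·π₀ / [0.05·π₀ + w·(1 − π₀)]

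Example with π₀ = 0.90 and w = 0.8: 0.045 / (0.045 + 0.080) = 0.36.

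| Assumed null share | Power 0.8 | Power 0.5 |
|---|---|---|
| 50% | 5.9% | 9.1% |
| 70% | 12.7% | 18.9% |
| 80% | 20.0% | 28.6% |
| 90% | 36.0% | 47.4% |
| 95% | 54.3% | 65.5% |

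Solving the formula for π₀, a false share of one third needs 83% null taxa (power 0.5) to 89% (power 0.8). One half needs 91% to 94%. If every taxon is null, 0.05 × 100 = 5 taxa are flagged per 100 tested.

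**Step 2: adding an FDR gate on the same data.** The simulation used 200 independent taxa, 1,000 runs per scenario, power 0.5 or 0.8, and correlation 0, 0.7 or 1 between the two test statistics. Cells give the range of the mean false share over power and correlation.

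| Null share | Raw P < 0.05 | Benjamini–Hochberg 0.05 | Both gates |
|---|---|---|---|
| 50% | 5.8–9.0% | 2.3–2.5% | 0.2–2.5% |
| 80% | 19.7–28.6% | 3.8–4.2% | 0.3–4.1% |
| 90% | 35.2–47.0% | 4.0–5.0% | 0.2–5.0% |
| 95% | 52.9–65.4% | 4.1–5.6% | 0.3–5.1% |
| 100% | 100% | 4.5–6.2% | 0.2–5.8% |

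Requiring both gates keeps the false share at about 6% or less, even though both tests use the same participants. This assumes that edgeR's p-values are valid.

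**Step 3: which case applies.** The article does not say. Step 1 describes LEfSe hits reported without edgeR confirmation, and all ranks above species. Step 2 describes species for which edgeR confirmation is required.

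**Limits.** The article gives no LDA-score cut-off. One would shorten the list in Step 1, but it would not set an error rate. The simulation treats taxa as independent.

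**The case against.** The strongest reply is that the sentence straight after LEfSe supplies an FDR gate. A reader who stops at the LEfSe sentence might infer that a third to a half of the reported taxa will be false. The documents do not support that. It needs roughly 83–94% null taxa, which the article does not state, and it ignores edgeR. Testing the same participants twice is not replication, but an FDR-controlled test still limits false discoveries in those data. This stands, and it confines the larger figures to hits that bypass edgeR.

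A reader might also infer that the two significance sentences contradict each other. That is too strong. The FDR sentence may apply only to comparisons of more than two categories, and the closing p < 0.05 may be the cut-off for p-values already adjusted where adjustment is specified. The two are unreconciled, not contradictory.

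Other points also stand. Multiplicity is handled for some comparisons of taxa and composition, including t-tests. The article never ranks LEfSe above ANCOM-BC. ANCOVA for confounders is planned. The limitations in Section 3 describe the study as hypothesis-generating, which lowers the stakes of a screening threshold.

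None of this says that a LEfSe hit must pass edgeR, covers ranks above species, or states which rule decides. A condensed article may leave detail to an analysis plan, but here it prints a specific unadjusted threshold.

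**Conclusion.** The point holds in limited form. LEfSe is stated at an unadjusted 0.05, out of step with the FDR control used elsewhere in the same section. The edgeR step is a same-sample second method for species only and is not a stated condition for reporting. The closing p < 0.05 is left unscoped.

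For LEfSe hits that bypass edgeR, the expected false share is about 6% to 65% over 50–95% null taxa and power 0.5–0.8, with 36% at 90% null and power 0.8. These inputs are assumptions, not figures from the article. Where both gates are required and edgeR's p-values are valid, it is about 6% or less. The article does not allow a single figure for the false share among reported taxa. This is an inexpensive improvement to the plan, not evidence that its results will be largely false.

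**What to change.** Before taxa are analysed, state one rule:

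- A taxon is declared associated only if its Benjamini–Hochberg q is below 0.05 over all taxa tested at that rank, in that niche (gut or oral) and for that contrast.
- Apply this to the Kruskal–Wallis p-values inside LEfSe and to two-group tests of taxa. Alternatively, label unadjusted LEfSe output as descriptive only.
- Describe edgeR as a sensitivity analysis on the same samples, not as validation.
- Limit the plain p < 0.05 in the final paragraph to single pre-named tests, such as Shannon index by Mediterranean diet adherence.

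Naming covariate-adjusted ANCOM-BC as the deciding method is a reasonable option, but it is not needed to close this point.

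The cost is wording only, and fewer taxa will be declared significant. No data collection or sample size changes.

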### 2.2. Study population

One thousand participants will be selected from users of Spanish primary healthcare centers who meet the following inclusion criteria: being aged between 45 and 74 years and not meeting any of the exclusion criteria, which include the following: cardiovascular disease; body mass index (BMI) > 40 kg/m^2^; severe renal failure; chronic inflammatory or bowel disease; oncology disease under treatment; terminal state; pregnancy; and use of antibiotics in the previous 2 weeks. Participants will be recruited at health centers with the active participation of family doctors and nurses.

The sample size for this study was calculated with the free software GRANMO (http://www.imim.cat/ofertadeserveis/software-public/granmo/). The size necessary to detect the difference of 0.1 points in the alpha diversity of the microbiota (Shannon index) between the subjects that do or do not meet the Mediterranean diet criteria has been estimated. The proportion of compliance with the Mediterranean diet in the Evident II study was 30% (29). Therefore, assuming an alpha risk of 0.05 and a beta risk of 0.2 in a two-sided test, a common standard deviation of 0.4 (30), and a 5% dropout rate due to technical difficulties or refusal to participate, 190 subjects in the first group and 436 in the second are required to detect a difference ≥0.1 point between them in the Shannon index. On the other hand, assuming a rate of exposure of 0.3% (dysbiosis), in the control group, 471 subjects with vascular aging and 471 controls are required to detect a minimum odds ratio of 1.5 in the study factor (alpha diversity). Therefore, the 1,000 participants to be included in the study will be enough to test the mentioned hypotheses and will have an equal gender distribution.

While patients did not participate in the design of the study, they will actively participate in recruitment by disseminating the study objectives and inclusion criteria through their organizations. At the end of the study, in addition to sending a detailed report with the results of each patient, a dissemination session will be organized for all patients included in the study. Through discussion groups, the opinions and experiences of the population regarding the influence of microbiota composition on health will be investigated. Similarly, their attitudes and possible resistance will be considered for the transfer to clinical practice.

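### The hurdle Poisson is chosen partly for overdispersion, but its count part cannot represent overdispersion among the positive counts, so its model-based p-values would be too small if the predicted overdispersion is present there

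*Protocol article*

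**What the plan says.** For the multivariate association of the microbiota with groups, section 2.4 (Bioinformatics and statistical analysis) names one model and gives the reason for it: "Zero-Hurdle Poisson Models (ZHP) will be adjusted given the predicted presence of excess zeros and overdispersion in the data". Excess zeros and overdispersion are listed as two separate features.

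For this model the section names no negative binomial count part, dispersion parameter, quasi-likelihood, robust variance or bootstrap. Similar tools appear nearby but belong to other analyses:

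- The random effects belong to the zero-inflated beta regression of oral and gut samples together.
- The bootstrap belongs to the mediation analysis.
- edgeR follows the LEfSe step: "These data will be validated using edgeR differential abundance analysis".

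Two significance rules are given. With the ANOVA comparisons: "A *p*-value of 0.05 adjusted for FDR will be considered statistically significant". At the end of the section: "A value of *p* < 0.05 will be considered statistically significant". The section does not say which of them governs the hurdle model.

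**The concern.** A hurdle Poisson has two parts. A binary part models zero against non-zero. A zero-truncated Poisson part models the counts above zero. The first part absorbs any number of excess zeros. The second has a single parameter, so the variance of the positive counts follows from their mean.

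The reason given for the model therefore covers only half of what it names. The hurdle removes overdispersion that comes from the zeros. It does nothing for positive counts that vary between people by more than a Poisson allows. In that case the maximum likelihood fit reports too much information and its standard errors are too small.

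At stake are the count-part p-values and confidence intervals, taxon by taxon, from the model named for the multivariate microbiota-by-group analysis. Section 3 (Discussion) gives the relation of lifestyles to the oral and gut microbiota as the main objective. An FDR procedure takes p-values as given, so it cannot correct ones that are already too small.

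**Working it through.** The documents give no figure for this model, so there is none to reproduce. The check is a formula followed by a simulation with no true group difference.

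**Inputs from the documents**

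- Total sample, section 2.2: "One thousand participants will be selected from users of Spanish primary healthcare centers".
- Group split: the same section takes 30% adherence to the Mediterranean diet, so 0.30 × 1,000 = 300 against 700.
- Test level: 0.05. Sidedness is not stated for this analysis; two-sided is used.
- Scale of the counts, section 2.3.7.1, for the V5-V6 pilot: "with 25% of the samples reaching over 100,000 reads". At 100,000 reads, a taxon at 0.1% abundance has 100,000 × 0.001 = 100 reads.

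**Assumptions, because the documents give no values**

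- 50% zeros in both groups.
- Positive counts are zero-truncated negative binomial with mean parameter μ from 5 to 500 and size k from 0.5 to 50. A smaller k means more overdispersion. A Poisson control was also run.

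**Formula**

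For a zero-truncated Poisson with parameter λ:

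- mean m = λ / (1 − e^(−λ))
- variance v = m(1 + λ − m)
- model-based variance of log λ from n positive counts = 1/(n·v)
- sandwich variance = s²/(n·v²), where s² is the observed variance of the positive counts

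The ratio of model-based to sandwich standard error is √(v/s²). For larger means v ≈ μ and s² ≈ μ + μ²/k, so the ratio is about 1/√(1 + μ/k). The null error rate of a nominal 5% Wald test is then about 2·Φ(−1.96 × ratio).

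- μ = 5, k = 10: 1/√1.5 = 0.82, error rate about 0.11
- μ = 20, k = 2: 1/√11 = 0.30, error rate about 0.55
- μ = 20, k = 1: 1/√21 = 0.22, error rate about 0.67
- μ = 100, k = 1: 1/√101 = 0.10, error rate about 0.85

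**Simulation** (300 against 700, 1,500 data sets per setting, Wald test of the count part)

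| μ | k | Error rate, model-based SE | Error rate, sandwich SE | Mean SE ratio |
|---|---|---|---|---|
| 5 | Poisson | 0.059 | 0.061 | 1.00 |
| 5 | 10 | 0.090 | 0.041 | 0.83 |
| 5 | 2 | 0.267 | 0.053 | 0.57 |
| 5 | 1 | 0.401 | 0.062 | 0.45 |
| 20 | Poisson | 0.052 | 0.055 | 1.00 |
| 20 | 10 | 0.242 | 0.050 | 0.58 |
| 20 | 2 | 0.545 | 0.045 | 0.31 |
| 20 | 1 | 0.661 | 0.055 | 0.23 |
| 100 | Poisson | 0.047 | 0.049 | 1.00 |
| 100 | 10 | 0.575 | 0.062 | 0.30 |
| 100 | 1 | 0.848 | 0.047 | 0.10 |
| 100 | 0.5 | 0.896 | 0.041 | 0.07 |

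The formula and the simulation agree closely. Over all settings run:

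- The sandwich test stays between 0.041 and 0.065.
- Without overdispersion in the positive counts, the model-based test stays between 0.047 and 0.059. The variance assumption is therefore the cause.
- The presence/absence part stays between 0.040 and 0.061.

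A second simulation of the same design gave 0.11 (μ = 5, k = 10), 0.58 (μ = 20, k = 2), 0.84 (μ = 100, k = 1) and 0.90 (μ = 100, k = 0.5) with model-based standard errors. In it, a hurdle negative binomial gave 0.04 to 0.065.

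**FDR adjustment**

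Two hundred null taxa were passed through Benjamini-Hochberg at 0.05, with 50 repeats. The mean number declared significant was 0.8 (μ = 5, k = 10), 99 (μ = 20, k = 2) and 166 (μ = 100, k = 1).

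**The case against.** There are four fair objections.

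- **The hurdle does handle some overdispersion.** The marginal variance of a hurdle Poisson need not equal its mean, so extra variance from the zeros is covered. This stands, and it makes the rationale incomplete rather than wholly false. The plan nevertheless lists overdispersion in addition to excess zeros, and the part within the positive counts stays uncovered.
- **The size is not known.** Means, dispersions and zero share are not in the documents. This stands. For rare, weakly dispersed taxa the excess is small. The severe figures need tens of reads or more together with marked dispersion. The pilot read depth makes such counts plausible but does not establish them: it describes a quarter of pilot samples, and rarefying would lower the counts.
- **It is one model among many.** ANCOM-BC, edgeR and the rank tests cover differential abundance without this defect. The sample-size hypotheses and the mediation analysis do not use the hurdle model. This stands. A reader might infer that all taxon-level results are compromised; the documents do not support that. The other methods are not, however, named as checks on the hurdle model, so they do not repair its own p-values.
- **An analysis plan may settle the variance.** The choice of variance estimator is commonly left to such a plan and its absence here is no fault. But the article fixes the Poisson form and gives overdispersion as a reason for it. That is a mismatch in what is stated, not a missing detail.

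**Conclusion.** The point holds in a conditional form. The plan predicts overdispersion and chooses a model whose count part cannot represent it among positive counts. If the prediction is right for those counts, model-based inference from the count part is anti-conservative. Under the assumed values the null error rate runs from about 10% to about 90%, rising with the mean count and with the degree of overdispersion. FDR adjustment does not cure this.

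Two stronger readings go too far. One is that the standard errors are certain to be far too small; that depends on dispersions the documents do not give. The other is that a hurdle Poisson cannot be used for inference at all; sandwich standard errors on the same fit restored the 5% level in every setting tried. The defect is confined to the count part of this one model.

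**What to change.** Reword the sentence in section 2.4 in one of two ways, and carry it into the analysis plan:

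1. Replace the hurdle Poisson with a hurdle negative binomial (zero-truncated negative binomial for the positive counts).
2. Keep the hurdle Poisson, and state that inference on the count part uses robust (sandwich) or bootstrap standard errors.

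State whether rarefied or unrarefied counts enter the model. If unrarefied, include log sequencing depth as an offset. A dispersion check on the positive counts would show how much the choice matters for each taxon.

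The first option costs one extra parameter per taxon. Both give wider intervals, which are the valid ones. No change to data collection or sample size is needed. Sandwich standard errors and the hurdle negative binomial were checked by simulation and held the level; the bootstrap was not simulated.
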